### Economic evaluation

A cost-effectiveness analysis (CEA) will be performed based on empirical data obtained in the study. The CEA will take a societal and health care perspective, involving direct medical (health care related), non-medical (travel, over the counter medication, time costs), and indirect (productivity) costs. The primary outcome measure in the CEA will be the PFDI-20, whereas cost-effectiveness will be expressed as costs per unit increase on the PFDI-20-scale. As most anatomical failures occur in the first year after surgery, we will assess the primary endpoint at 12 months after surgery. In line with the clinical endpoints, secondary outcome measures will be satisfaction with treatment and QALY, with cost-effectiveness ratios expressed as costs per woman satisfied with treatment and costs per QALY. The clinical outcomes will be derived from the trial data. Health state utilities to estimate QALYs will be derived from EQ-5D measurements at baseline, as well as 12 months. Utility values for EQ-5D scores will be based on Dutch estimates. The cost-utility analysis will estimate Incremental costs per QALYs will be calculated to determine cost-utility [54]. Costs will be calculated by multiplying resource use per patient with unit-cost estimates. Resource use will be obtained from trial records, complemented with patient administered cost-questionnaires. Unit costs will be based on publicly available standardized costs, fee schedules, and estimates reported in the medical literature. The choice of costing method will depend on the availability of appropriate cost estimates. Incremental costs and effects will be illustrated in a scatter plot to shown cost-effectiveness of the interventon as compared to control [54]. Neither costs nor effects will be discounted as the time horizon of the analyses is limited to 1 year. Sensitivity analyses will be performed to assess robustness of the results for uncertainties and assumptions regarding unit costs and resource use: bootstrap analysis (1000 replicates) will be used to estimate uncertainty [54]. Long term outcomes (for both costs and clinical outcomes) will be evaluated using modelling techniques. Consequences for the Dutch health care budget will be estimated in a budget impact analysis.

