### Outcome measures

The primary outcome is subjective improvement of POP symptoms at 1 year follow-up; the percentage of women with much or very much improvement of POP symptoms, measured with the Patient Global Impression of Improvement (PGI-I) scale [42]. PGI-I is a 7-point Likert scale, with scores ranging from very much worse to very much improved. Success is defined as ‘much or very much’ improvement.

Secondary outcomes are surgical success, POP-Q anatomy in all compartments, surgery related complications, general quality of life, disease specific quality of life (micturition and defecation), sexual function, signs and complaints of vaginal atrophy, vaginal pH, adverse events, costs, and adherence to treatment. Surgical success is defined as the absence of POP beyond the hymen (POP-Q at gynecological examination), the absence of bulge symptoms (absence of bulge symptoms is defined as a negative response to the question, “Do you see or feel a bulge in the vaginal area”), and absence of reoperation or additional pessary therapy for POP [43]. Follow up is scheduled at 6 weeks, 6 months and 12 months postoperative. Data will be collected using validated questionnaires (See also ‘Data collection’ and Fig. 1) and out-patient visits including gynecological examination are performed by an independent gynecologist.

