#### Questionnaires and diary

Participants will be asked to complete online questionnaires, generated in Castor EDC (when preferred, it is possible to complete the questionnaires on paper). Participants will receive 2 or more of the following questionnaires at baseline and 6 weeks, 6 months and 12 months postoperative (See also Fig. 1):Questionnaire on baseline characteristics and medical history (including age, length, weight, parity, education, history of diabetes, respiratory diseases and smoking, family history of POP).Patient Global Impression of Improvement (PGI-I): to assess subjective improvement of POP symptoms [42].EuroQoL (EQ-5D-5L): a general quality of life questionnaire, to evaluate health utilities and the corresponding quality adjusted life years (QALYs) [45].Pelvic Floor Disability Index-20 (PFDI-20): to measure symptom distress on disease specific quality of life, focusing on POP, urinary incontinence, and fecal incontinence [46].Pelvic Floor Impact Questionnaire-7 (PFIQ-7): to measure impact on specific quality of life, focusing on POP, urinary incontinence, and fecal incontinence [46].Most Bothersome Symptom questionnaire: to assess the most bothersome urogenital symptoms [47].The Pelvic organ prolapse Incontinence Sexual Questionnaire-IR (PISQ-IR): a condition-specific measure of sexual function in women with pelvic floor dysfunction, including urinary and anal incontinence and pelvic organ prolapse [48].Medical Consumption Questionnaire (iMCQ): for cost effectiveness analysis [49].Productivity Cost Questionnaire (iPCQ) to assess productivity loss [50].Adherence questionnaire: on adherence to treatment, experience using perioperative vaginal cream and influencing factors on compliance. This questionnaire has been developed for this study and is provided as Additional file 1.Adherence diary: a perioperative diary will be kept on the use of vaginal cream, from start till 6 weeks postoperative. Adverse reactions associated with vaginally administered estriol cream (e.g. temporary itch or irritation of the application site) can be reported in the diary as well.Adherence to treatment: Study medication will be delivered at the participant’s home address at two time points; 2 tubes at randomization and 3 tubes at 5 months post-randomization. Participants are asked to return the study medication at 5 months post-randomization and at the end of the study—12 months post-operative. In order to asses adherence to treatment, tubes will be weighted on a scale (Denver Instrument Company, TR-602, digit: 0.01 g) and recorded in Castor EDC.

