##### Secondary study parameters

All the secondary outcomes will be presented as frequencies with percentages for dichotomous outcomes, means with standard deviations for continuous normally distributed variables and medians with interquartile ranges for non-normally distributed variables.

We plan to calculate the differences within groups between baseline and 12 months using either a paired t-test, Wilcoxon signed rank test or McNemar test for PFIQ, PFDI-20, PISQ-IR, the compound measure, vaginal pH, vaginal atrophy (objective and subjective outcomes), adverse events, gynecological interventions performed, costs and compliance. Differences between groups (including relative risks with 95% confidence interval) will be analyzed using one-sample t-test for normally distributed numerical data, Mann–Whitney U tests for not normally distributed numerical data, chi-square testing for categorical data and Fisher’s exact testing for rare outcomes.

The secondary outcome quality of life at 1 year after the procedure, will be measured with the EQ-5D-5L and will be analyzed using the utility calculation that was used in other studies [51]. Quality of life outcomes will be described and analyzed accordingly. Difference in utilities between groups will be estimated using a linear regression. For each time point, QALYs will be calculated by multiplying the utilities by time (as fraction of a year) [52, 53]. Results will be further incorporated in the cost-effectiveness analyses.

Adherence to therapy will be assessed by comparing tube weights to the anticipated weight if used according to protocol. Participants will also keep a perioperative diary on the use of vaginal cream to calculate adherence to therapy until 6 weeks postoperative. Moreover, adherence to therapy will be calculated at 6 and 12 months postoperative from the adherence questionnaire.

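### The article gives two unreconciled QALY rules; the baseline-and-12-month rule can misstate the incremental QALY in either direction

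*Protocol article*

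**What the plan says.** Three parts of the protocol article bear on this.

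- **Economic evaluation:** "Health state utilities to estimate QALYs will be derived from EQ-5D measurements at baseline, as well as 12 months". The same section sets the horizon: "Neither costs nor effects will be discounted as the time horizon of the analyses is limited to 1 year". The PFDI-20 is the primary outcome of the cost-effectiveness analysis. The QALY is one of two secondary outcomes there, the other being satisfaction with treatment.
- **Secondary study parameters (Data analysis):** "For each time point, QALYs will be calculated by multiplying the utilities by time (as fraction of a year"). The time points are not listed. The section then adds: "Results will be further incorporated in the cost-effectiveness analyses".
- **Questionnaires and diary:** "Participants will receive 2 or more of the following questionnaires at baseline and 6 weeks, 6 months and 12 months postoperative". The EQ-5D-5L is on that list, described as "a general quality of life questionnaire, to evaluate health utilities and the corresponding quality adjusted life years (QALYs". The visits that carry it are given only in Fig. 1, which is not shown.

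**The concern.** The same quantity is defined twice. One section builds the QALY from two EQ-5D measurements. The other builds it at each time point, in an article whose follow-up is at 6 weeks, 6 months and 12 months, and sends the result into the same economic analysis. An analyst cannot tell which measurements enter the QALY.

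The choice matters because a two-point QALY assumes that the between-arm difference in utility moves in a straight line from baseline to 12 months. The trial has reasons to expect other shapes. The Background argues from wound healing, and the recorded surgical complications include hematoma, urinary retention and urinary tract infection, which may differ between arms early and then resolve. The hypothesis of fewer recurrences and reoperations could instead produce a difference that appears late. Costs are accumulated over the whole period, including unscheduled visits. Under the two-point rule, the cost-per-QALY ratio would therefore set a year of recorded resource use against two snapshots of utility.

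**Working it through.** **No figure to reproduce.** The article gives no utility difference, incremental QALY or cost per QALY, so the check is in units of d, an assumed full between-arm difference in utility.

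**Inputs**
- Time points: baseline, 6 weeks, 6 months and 12 months (Outcome measures; Questionnaires and diary).
- Horizon: 1 year (Economic evaluation). Times in years are therefore 0, 6/52 = 0.1154, 0.5 and 1.
- Assumptions: no arm difference at baseline, and EQ-5D available at all four points.

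**Formulas.** Write D6w, D6m and D12 for the arm difference in utility at each visit. The trapezoidal weight of an inner point is half the distance between its neighbours, and that of the last point is half the last interval.
- D6w: (0.5 − 0)/2 = 0.25
- D6m: (1 − 0.1154)/2 = 0.4423
- D12: (1 − 0.5)/2 = 0.25

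Four points: ΔQALY = 0.25·D6w + 0.4423·D6m + 0.25·D12.

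Two points: ΔQALY = 0.5·D12, whatever happens in between.

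**Results**

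| Course of the difference | Four points | Two points | Two / four |
|---|---|---|---|
| Full by 6 weeks, sustained | 0.942d | 0.500d | 53% |
| Half at 6 weeks, full from 6 months | 0.817d | 0.500d | 61% |
| None at 6 weeks, full from 6 months | 0.692d | 0.500d | 72% |
| Linear growth | 0.500d | 0.500d | 100% |
| At 12 months only | 0.250d | 0.500d | 200% |
| At 6 weeks only | 0.250d | 0 | 0% |
| At 6 months only | 0.442d | 0 | 0% |
| At 6 weeks and 6 months, gone by 12 months | 0.692d | 0 | 0% |

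For the same cost difference, the first row overstates cost per QALY by 0.942/0.500 = 1.88 times, and the 12-months-only row halves it. In the last three rows the two-point ratio has a zero denominator. With d = 0.05, chosen only for illustration, the first row is 0.047 against 0.025 QALY.

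**Common dip.** If surgery lowers utility by c in both arms, the difference is (uE − c) − (uP − c) = uE − uP. A shared dip and recovery therefore does not bias the increment; only a difference between arms in that course does.

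**Baseline imbalance.** A chance baseline difference b enters with weight 0.1154/2 = 0.058 under four points and 0.5 under two. This is a reason to put baseline utility in the regression.

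**Horizon.** The Interventions section has 4 to 6 weeks of treatment before surgery and 52 weeks after it, which makes 56 to 58 weeks. If the baseline EQ-5D goes with the first hospital visit, which precedes study medication, the interval from baseline to 12 months after surgery is longer than the stated 1 year. On a 58-week axis (0, 12, 32 and 58 weeks, divided by 52), the sustained case is (6 + 20 + 26)/52 = 1.000d with four points and 29/52 = 0.558d with two, a ratio of 56%.

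**The case against.** The strongest reply is that the article does not fix a two-point rule. The each-time-point sentence explicitly feeds the cost-effectiveness analysis, so the shorter sentence in the economic section may be loose wording. That is why the finding is a conflict between two sections and not a settled error. The conflict itself stands, because the economic section names its measurements and omits the intermediate ones.

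A reader might infer that the plan throws away EQ-5D data from 6 weeks and 6 months. The text does not support this. Each visit carries only a subset of the questionnaires, and Fig. 1 is not shown. If the EQ-5D is taken only at baseline and 12 months, nothing is discarded, the economic section is accurate, and the each-time-point wording is what needs correcting.

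A reader might also infer that the QALY gain will be halved. That is roughly the result for the most favourable sustained course only. A late benefit gives the opposite error, and the article states no time course.

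Two further readings go too far. Multiplying utility by time need not mean a step function: the sentence is a one-line summary citing methods papers that are not at hand. The absence of a stated baseline adjustment is not a defect of the article either, since covariates are commonly left to the analysis plan.

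**Conclusion.** The point holds as an unreconciled definition. If the Economic evaluation wording is followed and the arm difference does not grow linearly, the incremental QALY is misstated. In the courses examined, the two-point result ranges from zero, when a real gain has gone by 12 months, to twice the four-point value, when the gain is seen only at 12 months. An early sustained difference keeps 53%. The direction cannot be known in advance.

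The reach is limited to the secondary cost-per-QALY result. The PGI-I primary outcome, the sample size and the cost per PFDI-20 unit are untouched.

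The sizes rest on no baseline difference, trapezoidal interpolation as the reference, and EQ-5D collection at both 6 weeks and 6 months. If only the 6-month measurement is added, the sustained case becomes 0.5d + 0.25d = 0.75d against 0.50d. If neither is collected, the contradiction in wording remains and the weakness lies in the measurement schedule.

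**What to change.** State one rule in both Secondary study parameters and Economic evaluation:

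1. Name the visits at which the EQ-5D-5L is given.
2. Calculate each woman's QALY as the trapezoidal area under the curve through every EQ-5D-5L measurement the trial collects over the stated horizon.
3. Estimate the between-arm QALY difference by regression on arm and baseline utility.
4. Align the horizon with the baseline measurement: say whether the year runs from baseline or from surgery, how the preoperative treatment weeks are handled, and use the same window for costs.

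If the EQ-5D is already given at 6 weeks or 6 months, this costs only wording in the analysis or health-economics plan, settled before unblinding. If it is not, correct the each-time-point sentence and report the straight-line assumption as a limitation of the cost-utility result. Adding measurements would then be new data collection, with its own burden.

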### Randomization

Women will be randomized in a 1:1 ratio to perioperative treatment with estriol or perioperative treatment with placebo using computer-generated randomly permuted blocks of sizes 4, 6 and 8. Blinded randomization will be performed by the participating center using online software (Castor Electronic Data Capture, Amsterdam, the Netherlands [online] available at: http://castoredc.com). The central coordinating pharmacy of the Academic Medical Center Amsterdam receives an automatically generated email containing the allocated treatment for each randomized patient from the Castor system. After also receiving a doctor’s prescription, the pharmacy will deliver study medication at the participant’s home address by courier service.

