### Data collection

All data will be systematically recorded by trained research nurses or gynecologists in an electronic Case Report Form in web-based data management software: Castor EDC. Castor EDC allows researchers to collect and manage data in accordance with the GCP guidelines [44]. To improve data quality, range checks are incorporated in the electronic Case Report Form. The software will randomly assign an unique numeric code for every subject that bears no relation to initials or date of birth. Data handling will be done with coded data, with the key (code to personal information linkage) only available to the local investigator and the research nurse working in the participating center. Persons who have access to the coded data include: investigators, research staff, monitoring and quality assurance personal. Data will be preserved for the duration of 15 years. The handling of personal data complies with the European General Data Protection Regulation. Participants will be followed from baseline (pre-operatively) up to 1 year after POP surgery. During the follow up period the following data will be collected:

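### The QALY includes the pre-treatment EQ-5D value and no baseline adjustment is stated, so the incremental QALY carries chance imbalance and is less precise than the collected data allow

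*Protocol article*

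**What the plan says.** On the inputs to the QALY, Economic evaluation states: "Health state utilities to estimate QALYs will be derived from EQ-5D measurements at baseline, as well as 12 months". Secondary study parameters gives the construction: "For each time point, QALYs will be calculated by multiplying the utilities by time (as fraction of a year". It does not spell out weights or interpolation.

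On timing, Data collection states: "Participants will be followed from baseline (pre-operatively) up to 1 year after POP surgery". Hospital visits places the first study visit before study medication is started.

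On the comparison between arms, Secondary study parameters states: "Difference in utilities between groups will be estimated using a linear regression". That sentence concerns utilities and lists no covariates. The other between-group methods in the section are unadjusted tests. Data analysis mentions possible confounders and gives withdrawal and missing data as examples.

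On use of the result, Economic evaluation plans incremental costs per QALY and a scatter plot of incremental costs and effects, and adds: "bootstrap analysis (1000 replicates) will be used to estimate uncertainty". QALY is not the lead outcome there. The primary measure of that analysis is the PFDI-20, and "secondary outcome measures will be satisfaction with treatment and QALY".

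**The concern.** A utility measured before treatment cannot carry a treatment effect, so within a QALY it contributes only variation between women. If the arms happen to differ at baseline, that difference passes into the incremental QALY with whatever weight the baseline visit has. It also passes in indirectly, because later utilities are correlated with the baseline value. Regressing on baseline utility removes both parts.

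The incremental QALY is the denominator of the cost-per-QALY ratio and one axis of the scatter plot. One year of follow-up after prolapse surgery is likely to produce a small QALY difference, so avoidable noise there makes the ratio unstable. The bootstrap would show the extra width, but it resamples the women actually enrolled and so stays centred on a difference that includes their baseline imbalance.

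**Working it through.** **Inputs from the protocol article.** EQ-5D at baseline and 12 months, a horizon of 1 year and a 1000-replicate bootstrap (Economic evaluation); 1:1 allocation (Randomization); 150 women per arm with 10% loss (Sample size), so 150 × 0.9 = 135 analysed per arm.

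The article states no standard error, SD or correlation for EQ-5D or QALYs, so there is no stated QALY figure to reproduce. Its 136 per arm is for the PGI-I. It does reproduce: (0.80×0.20 + 0.65×0.35) × (1.960 + 0.842)² / 0.15² = 135.2, rounded up to 136. It matters here only through the number of women.

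**Assumptions.** Utility SD 0.20 at each visit (range 0.15 to 0.25); correlation rho between visits 0.5 (range 0.3 to 0.6, with 0 as a floor); QALY as a trapezoid area; baseline questionnaire completed before the first dose of cream.

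**Two-point QALY.** Q = (u0 + u12)/2, so baseline has weight 0.5.

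- Unadjusted variance per woman: SD²(1 + rho)/2. At rho 0.5: 0.04 × 1.5/2 = 0.030. SE of the difference: sqrt(2 × 0.030/135) = 0.0211.
- Variance after regression on u0: SD²(1 − rho²)/4. At rho 0.5: 0.04 × 0.75/4 = 0.0075. SE: sqrt(2 × 0.0075/135) = 0.0105.
- Ratio of SEs: sqrt(2/(1 − rho)), which does not depend on the SD or the sample size.

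**Four-visit QALY over one year.** With visits at 0, 6/52, 0.5 and 1 year, the trapezoid weights are 0.058, 0.250, 0.442 and 0.250, and the squared weights sum to 0.324. At rho 0.5, in units of SD²:

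- unadjusted variance: 0.5 + 0.5 × 0.324 = 0.662;
- covariance with baseline: 0.058 + 0.5 × 0.942 = 0.529;
- adjusted variance: 0.662 − 0.529² = 0.382;
- ratio: sqrt(0.662/0.382) = 1.32.

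| rho | Two-point SE, unadjusted | Two-point SE, adjusted | Two-point ratio | Four-visit ratio |
|---|---|---|---|---|
| 0 | 0.0172 | 0.0122 | 1.41 | 1.01 |
| 0.3 | 0.0196 | 0.0116 | 1.69 | 1.13 |
| 0.5 | 0.0211 | 0.0105 | 2.00 | 1.32 |
| 0.6 | 0.0218 | 0.0097 | 2.24 | 1.46 |

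**Sensitivity.** The SEs scale with the SD: at rho 0.5 and SD 0.15 to 0.25, the two-point values run from 0.0158 to 0.0264 unadjusted and from 0.0079 to 0.0132 adjusted. Unequal SDs change the ratio. At rho 0.5 it is 1.76 if the SD is 0.15 at baseline and 0.20 at 12 months, and 2.34 if these are reversed.

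**Chance imbalance.** The SE of the baseline difference is 0.20 × sqrt(2/135) = 0.0243, so its 95% range is ±1.96 × 0.0243 = ±0.048. Half of that, ±0.024 QALY, enters the two-point difference directly.

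**Simulation check.** With rho 0.5, no treatment effect and 10,000 repetitions, the mean difference was 0.0002 unadjusted and 0.0001 adjusted, both practically zero. The SDs were 0.0213 and 0.0106, a ratio of 2.00.

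**The case against.** The strongest reply is that a condensed article is silent on covariates, and silence is not a decision. A linear regression is named for utilities; it excludes no covariate and could hold the baseline value. Covariate lists and bootstrap details often sit in a full protocol or health-economic plan, and none is shown. This stands: a reader might infer that the trial chose not to adjust, and the article does not say so. What remains is that the article itself puts a pre-treatment measurement into the outcome and gives no step that takes it out. The regression it names is for utilities, not QALYs.

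A reader might also infer that the cost-utility result is biased. It is not: "Women will be randomized in a 1:1 ratio", so the unadjusted difference is right on average. The loss is in precision and in exposure to the imbalance that happens to arise.

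Nor is a doubling of the standard error a ceiling. The two-point ratio passes 2 once the correlation exceeds 0.5, and it is well below 2 if four visits are used. The trapezoid itself is inferred. Whether EQ-5D is given at the intermediate visits is also unconfirmed, because the text says only "Participants will receive 2 or more of the following questionnaires at baseline and 6 weeks, 6 months and 12 months postoperative" and the schedule figure is not shown.

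Finally, adjustment will not make a small effect easy to see. If each extra success were worth 0.10 utility (an assumption), the planned 15-point difference would give 0.15 × 0.10 × 0.5 = 0.0075 QALY by the two-point calculation. That is below even the adjusted SE of 0.0105. This limits what the change can achieve, but it is no reason to keep the noisier estimate.

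**Conclusion.** The point holds as a matter of efficiency and clarity. As written, the plan builds QALYs partly from a pre-treatment value and states no adjustment for it. Followed literally, it gives an unbiased incremental QALY with a standard error about 1.7 to 2.2 times the adjusted one for correlations of 0.3 to 0.6 in the two-point QALY, and 1.4 times even at zero correlation. With four visits over one year the factor is about 1.1 to 1.5 over the same range.

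These sizes rest on assumed correlations, equal SDs, a trapezoid QALY and a baseline questionnaire completed before treatment. The direction does not depend on the particular SD or correlation chosen. QALY is a secondary outcome of the economic evaluation; the trial's primary endpoint (PGI-I) and the PFDI-20 cost-effectiveness ratio are not affected. This is an improvement worth making, not a flaw that invalidates the plan.

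**What to change.** In Economic evaluation, or in the health-economic analysis plan if there is one, state that:

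- the incremental QALY is the arm coefficient from a linear regression of each woman's QALY on treatment arm and baseline EQ-5D utility;
- this regression is refitted in each of the 1000 bootstrap replicates and paired with the cost difference from the same replicate, so that the correlation between costs and effects is kept;
- the adjusted value is used in the cost-per-QALY ratio and the scatter plot, with the unadjusted value shown alongside.

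The cost is a few lines of text and one covariate. Baseline EQ-5D is already collected, so no new data are needed. If an unshown plan already specifies this, a sentence saying so settles the matter.
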